### **C. Study Design and Research Methods**

Similar to our previous protocols, we will conduct a 2-arm randomized controlled trial evaluating if wearing a Smartwatch and having access to its data improves well-being, and if so which well-being dimensions. Additionally, we will collect continuous physiological measures (measured from Smartwatches) to determine if they contain a 'signal' that predicts physician well-being, and if so in which dimensions. Findings will be shared as generalizable knowledge through peer-reviewed publications and presentations.

Administrative records will be used to identify physicians employed by University of Colorado School of Medicine and Mayo Clinic. Participants will be recruited through electronic communications, flyers, and announcements (see scripts). No more than 3 e-mails will be sent. In partnership with leadership, investigators and trained research staff will recruit potential study participants by email using administrative rosters, which contain information on primary work units assigned and email addresses. We will also liaison with management for more informal recruitment efforts. This will include advertising by internet (intranet only), flyers, and by oral presentations at work unit meetings (by invitation only). We will explain the aims of the study and summarize the research procedures. Opportunities to address questions and potential concerns will be provided.

Those are interested in study participation can contact the study team using the contact information listed on advertising materials, or they can scan a QR code or click on a URL link that takes them to a web form (in MS Forms or Qualtrics) that contains information about the study and a screening form. Study coordinators will review the screening form and send an email to

eligible physicians, inviting them to enroll in the study by reading and electronically signing the consent form. (see consent form). If the physician has additional questions, they may contact the PI, co-investigator, or study coordinator. Information collected by the screening form for physicians who opt not to join the study will be deleted.

We anticipate recruitment will take no longer than 3 months.

Once we have recruited the appropriate number of physicians, we will administer the baseline survey. After completion of the baseline survey, Consented physicians will be randomly assigned via computer-generated algorithm to one of two groups: Arm 1 = Smartwatch Intervention; Arm 2 = Control. Randomization will be stratified by gender, specialty, work site, and physician category (resident or physician in-practice) using permuted blocks.

Participants randomized to the Smartwatch Intervention arm will receive a Garmin Smartwatch after enrollment and completion of the baseline survey. Garmin Smartwatches are sleek and provide the broadest range of all-day health monitoring features to keep track of energy levels, pulse oximetry, respiratory rate, stress levels, sleep patterns, and heart rate while operating with 18-hour battery life per charge cycle. Participants will be asked to wear the Garmin watch much as possible during the 12-month study period.

Participants randomized to the Control arm will receive no intervention for the first six months of the study, at which point they will receive Garmin Smartwatches after completion of the 6 month survey.

**Smartwatch Issuance.** Study subjects will be issued a Garmin Venu 2 Plus or Venu 3s smartwatch (control group subjects will receive the Venu 3s model). For these procedures, trained research staff will de-identify subjects (subject ID and anonymized number ID maintained by PIs) and enroll them into Garmin Connect (for collecting data from Garmin smartwatches) and Fitabase. The study coordinator will work with each subject to identify the best way (time and place) to deliver their smartwatch. At the time of delivery, subjects will also receive a printed manual with step-by-step instructions for setting up linkages with Garmin and Fitabase. Prior to delivery, each subject will also receive an individualized email with a unique link needed for setting up the Fitabase data extractor.

Research staff will train subjects on the use and basic maintenance of the smartwatches. Subjects will be informed that research staff can be contacted any time questions arise about the basic operation and maintenance of the smartwatches. Contact information for research staff will be provided.

Study team will promote engagement through bi-weekly in person visits or email as a way to remind regular synchronization of their watch data or completion of quarterly surveys.

Study team will also disseminate a periodic newsletter upon IRB approval (each time), wherein study progress, aggregate data collected (e.g., cumulative statistics on sleep, hours of data, and wear-time), and sample statistics (e.g., unit-level total numbers) are reported. We will also

feature a participant's experience (e.g., positive experience with watch, or an anecdote) only if they consent to sharing – with the following message below. We will provide the participant the option to not be identified, or if they choose to be identified, we will provide the disclaimer also stated below.

Dear participants, **welcome** to the 1st edition of our newsletters! We want to use this newsletter as a fun way to share **your** experiences and thoughts during the study. *If you have anything to share about your experiences in the study such as fun stories, photos or anecdotes – we want to hear from you! While the newsletter is broadcasted to participants of the study, we cannot guarantee the contents of the newsletter will not be shared to others by participants. If you want to share anything for our newsletters, and we decide to feature it, we will send the final version of the newsletter for your approval before it is released. If you have a story idea, please email it to [name] ([contact]).*

All participants will be asked to complete surveys at baseline and at 3-, 6-, 9- and 12-months (see cover letters). We will use MS Excel for maintaining a list of participants, device serial number and basic information (e.g., department). The quarterly surveys will be collected via Mayo Clinic's Survey Research Center, which stores data from Qualtrics. Trained research staff will follow-up via phone if survey not completed within 7 days of the first alert.

The surveys will include the validated Well-Being Index, Maslach Burnout Inventory, Linear Analogue Self-Assessment quality of life scale, Perceived Stress Scale, and Epworth Sleepiness Scale, and Quick Inventory of Depressive Symptoms (QIDS-SR). No instrument or question in this survey is designed to diagnose depression or screen for major depressive disorder or suicidality. Each of these metrics has been validated across a wide range of medical conditions and populations, including physicians. Additional self-reported items will explore workplace factors (e.g., work hours, call frequency, shift work, work location [inpatient, outpatient, surgical], etc.), self-reported medical error, and use of organizational provided stress management and fatigue mitigation strategies. Items can be found in the Survey Instrument document. As a token of appreciation, participants will receive \$25 for each survey completed.

Finally, smartwatch data (energy levels, respiratory rate, stress levels, sleep patterns, and heart rate) will be collected via FitaBase - a 3rd party data aggregator which will not collect any PHI. We have already tested and developed a parser to query Garmin's system every 14-days, download the raw data, and process them for analyses by summarizing the sensor features by the minute, hour, day, week or month and store into REDCap database.

During the final quarter of the study, March 1-May 31,2024 participants who wear their watches for an average of 70% of the time will receive a \$25 e-gift card. This purpose of this incentive is to maximize data to enhance analysis. The data analytic methods rely on complete data for meaningful predictions and can only handle data missingness up to 30%. The wear time goal reflects the threshold needed for data analysis. Wear time will be measured by the watch based on detected heart rate. Participants will be notified of the incentive through the regular newsletter.

During the final quarter of the study, March 1-May 31,2024 participants who wear their watches for an average of 70% of the time will receive a \$25 e-gift card. This purpose of this incentive is to

maximize data to enhance analysis. The data analytic methods rely on complete data for meaningful predictions and can only handle data missingness up to 30%. The wear time goal reflects the threshold needed for data analysis. Wear time will be measured by the watch based on detected heart rate. Participants will be notified of the incentive through the regular newsletter.

As the study progresses, we will collect physiologic data from the Smartwatches and build the data infrastructure (Aim 2), and as data accumulates, develop predictive models for burnout (3) using data from the intervention cohort (development cohort for the prediction model) followed by data from the control cohort (validation cohort). To complete this work, we will leverage expertise in computer engineering, machine learning, and artificial intelligence to develop an analytical framework that combines probabilistic graphical models (PGMs) and multitask learning (MTL) to derive interpretable predictions of burnout.

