**Hypothesis:**

1. Physicians with individualized access to their energy levels, oxygen level, respiratory rate, stress levels, sleep patterns, and heart rate will engage more frequently in behaviors that mitigate stress, resulting in improved well-being.
2. Fatigue, stress, and overall quality of life will improve while burnout will be less impacted by wearing a Smartwatch.
3. Physiologic parameters, collected from Smartwatches, will relate to physician's subsequent endorsement of symptoms of fatigue, stress level, and overall quality of life more closely than their measured symptoms of professional burnout.

In this study, physicians will be asked to wear a Smartwatch and answer a survey at baseline, 3-, 6-, 9-, and 12-months. We will determine if physicians who wear a Smartwatch and have access to its data experience greater improvements in their well-being relative to physicians not wearing a Smartwatch (control group). In addition, we will collect data from the Smartwatches to determine if we can utilize this data to predict subsequent level of well-being. We will build the

infrastructure and a HIPAA compliant de-identified dataset which includes (i) continuous physiology measures (from Smartwatches; raw data gathered for every 15-second epoch) and (ii) survey responses. We will use this dataset to develop predictive models for well-being derived from physiologic measures. Prediction models established using the cohort in Arm 1 will be validated in the cohort in Arm 2 after they cross-over (at the 6-month time-point) and begin using the Smartwatch.

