#### **F. Data Analysis Plan:**

For Aim 1, we will compare changes in outcome variables between Arm 1 (Smartwatch Intervention) and Arm 2 (Control group) at 6 months. Then, we will explore the durability of the benefits of having a Smartwatch for 12 months, by examining levels of well-being among Arm 1 participants at the 6- and 12-month mark. We will use generalized estimating equations to account for the repeated-measures design. Tests will be 2-sided, and we will use the intent-to-treat principle in analyses.

To determine whether continuous physiological measures (measured from Smartwatches) contain a 'signal' that predicts physician well-being, and if so in which dimensions. We will construct Probabilistic Graph Models (PGMs) for low overall well-being (score  $\geq 2$ ), burnout (score of  $\geq 27$  on emotional exhaustion scale or score of  $\geq 10$  on the depersonalization score), low quality of life ( $\geq \frac{1}{2}$  SD below the mean), high stress (score  $\geq 17$ ), and high fatigue (score  $\geq 11$ ). We will derive dynamics for these dimensions of well-being using dynamic Bayesian networks (DBN). Data from Arm 1 will be used to train MTL models to predict risk of low well-being, burnout, low QOL, high stress, and high fatigue in the next quarter. Models will be tested and retrained using data from subsequent assessments. We will then evaluate the predictions using data from Arm 2 (control). Standard metrics of model performance (e.g., AUC, sensitivity, specificity) will be reported. Predictor variables will be ranked by the relative importance in making predictions, and the top 10 predictors (a heuristic for simplicity in deriving easily interpretable predictions in English sentences) will comprise Core Well-being Factors. We aim to achieve predictive accuracies > 70%.

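### Watch model follows trial arm, so validating the Arm 1 prediction models in Arm 2 is wholly or partly a cross-device test, and a weak result could not be clearly read as absence of signal

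*Protocol*

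**What the plan says.** Section IV.C, under Smartwatch Issuance, provides for two watch models and fixes one of them for the control arm: "Study subjects will be issued a Garmin Venu 2 Plus or Venu 3s smartwatch (control group subjects will receive the Venu 3s model". It does not say how the two models are divided within Arm 1.

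Three places set the roles of the arms in Aim 2:

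- Section I (Hypothesis): "Prediction models established using the cohort in Arm 1 will be validated in the cohort in Arm 2 after they cross-over".
- Section IV.C: models are built "using data from the intervention cohort (development cohort for the prediction model) followed by data from the control cohort (validation cohort".
- Section IV.F: after training in Arm 1, "We will then evaluate the predictions using data from Arm 2 (control". Between those two steps stands one sentence: "Models will be tested and retrained using data from subsequent assessments".

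The predictors come from the watch: "smartwatch data (energy levels, respiratory rate, stress levels, sleep patterns, and heart rate) will be collected via FitaBase" (section IV.C). Section IV.D lists the analysis inputs as participant ID, sex, watch data and survey scores; watch model is not among them. Device serial numbers are kept in the participant list (sections IV.C and IV.D). Section IV.F names AUC, sensitivity and specificity as example metrics and sets a target: "We aim to achieve predictive accuracies > 70" per cent.

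**The concern.** Validation in a separate arm is meant to show whether a model carries over to people it has not seen. Here the new people also wear a watch model that some or all of the training participants did not wear. If the two watch models record or summarise sleep, stress, energy or heart rate differently, the loss of performance from that change is mixed with any loss from a model that does not generalise.

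Aim 2 asks whether the watch data contain a signal for well-being. A weak Arm 2 result would invite the answer no, and the design as written gives no same-device result in new people to set against it. Only the negative direction is affected: a model that performs well in Arm 2 has held up across people and, at least in part, across devices.

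**Working it through.** **1. Where each test sits.** From sections I, IV.C and IV.F:

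| Planned test | People | Watch model |
|---|---|---|
| Later assessments (IV.F), read as Arm 1 because the sentence sits between Arm 1 training and Arm 2 evaluation | Same people as in training | Same as in training |
| Arm 2 after cross-over | New people | Venu 3s only |
| Not described | New people | Training mix, including any Venu 2 Plus |

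The third row is the missing comparison. No person outside the training set is ever tested on a Venu 2 Plus.

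**2. How far arm and device can be separated.** Let p be the share of Arm 1 wearing the Venu 3s; the protocol gives no value. Assume equal arms. With every Arm 2 participant on the Venu 3s, the correlation of arm with device is r = √[(1 − p)/(1 + p)], and the variance inflation factor is 1/(1 − r²) = (1 + p)/(2p).

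| Assumed p | r | Variance inflation |
|---|---|---|
| 0 | 1.00 | infinite |
| 0.10 | 0.905 | 5.5 |
| 0.25 | 0.775 | 2.5 |
| 0.50 | 0.577 | 1.5 |

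At p = 0 no analysis of Arm 2 can tell device from arm. At any other p they are partly separable, but only if watch model is carried into the analysis.

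**3. What a device difference would look like.** The protocol states no device effect, so this is an illustration. Take a normally distributed risk score with equal variances and equal numbers of cases and non-cases, and a cut-off fixed in Arm 1. Assume 75% accuracy in Arm 1. Then d = 2 × Φ⁻¹(0.75) = 1.35 and AUC = Φ(d/√2) = 0.83.

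*Added device noise* multiplies the score SD by k, so d becomes d/k:

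| k | d/k | Accuracy Φ(d/2k) | AUC |
|---|---|---|---|
| 1.25 | 1.08 | 70.5% | 0.78 |
| 1.5 | 0.90 | 67.4% | 0.74 |
| 2.0 | 0.67 | 63.2% | 0.68 |

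Each row is identical to a truly weaker model with that smaller d. Nothing in the Arm 2 metrics would tell them apart.

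*A constant device offset* of s SD gives sensitivity Φ(d/2 + s) and specificity Φ(d/2 − s). At s = 0.75 these are 92.3% and 47.0%. Accuracy is (92.3 + 47.0)/2, about 69.6% before rounding of the components, just below the 70% target. AUC stays at 0.83. With equal numbers of cases and non-cases, an offset of the opposite sign gives the same accuracy.

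A pure offset therefore leaves a trace (AUC intact, sensitivity and specificity pulled apart), whereas added noise does not.

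**The case against.** The strongest reply is that nothing in the protocol shows the two watch models to measure differently. Section I describes raw data in 15-second epochs, and section IV.C describes a study parser that summarises them. A reader might infer that a device shift enters every Arm 2 record; the documents do not support that as fact. It remains a possibility that the plan leaves unexamined.

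A reader might also infer that device and arm are fully confounded. That holds only if no Arm 1 participant wears a Venu 3s, and the text does not say so.

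Nor would a weak Arm 2 result always be unreadable. A constant offset leaves AUC untouched, and AUC is among the planned metrics. An offset need not lower accuracy either. With AUC 0.70 and an assumed 30.9% prevalence (the normal-theory share lying half an SD or more below the mean, the protocol's quality-of-life cut-off), accuracy of 64.5% falls to 56.0% for +0.5 SD but rises to 69.7% for −0.5 SD. Accuracy alone is thus a poor guide to harm.

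The final-quarter payment ("participants who wear their watches for an average of 70% of the time will receive a" gift card) covers 3 of about 6 wear months in Arm 2 against 3 of 12 in Arm 1, and might look like a second bias. The calendar quarter and threshold are the same for both arms, the stated purpose is more complete data, and no harm to validation is shown. It is not part of this point.

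Finally, resampling and reporting by device are often left to an analysis plan, and section IV.F does not rule out cross-validation by participant. That stands, and makes this an improvement rather than an error. What remains is that the protocol itself ties device to arm and validation to arm; if Arm 1 has no Venu 3s, no later analysis of Arm 2 undoes that.

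**Conclusion.** The point holds in a limited form. The boundary between training and validation is wholly or partly a device boundary, and as written there is no test in new people on the training mix of devices. If the two watch models measure differently, a failed or weakened Arm 2 validation could not be clearly attributed to absent signal.

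The size cannot be computed from the documents, which give neither a device effect nor the Arm 1 split. Under the assumptions shown, an increase of one quarter to double in the score SD would take 75% accuracy to between 70.5% and 63.2%, indistinguishable from a weaker model.

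Three limits apply. A successful Arm 2 validation would still support the model. Aim 1 is unaffected, because controls have no study watch until after the 6-month survey. And the cohorts also differ in calendar period and length of wear, so a gap between Arm 1 and Arm 2 performance would not by itself prove a device effect. This is a cheap improvement to Aim 2, not a flaw that invalidates it.

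**What to change.** Keep the devices and the arms, and change the analysis:

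1. State how many Arm 1 participants received each watch model, and derive the model for every participant from the recorded serial numbers as an analysis variable.
2. Add participant-level cross-validation within Arm 1, with no person in both training and test, as the same-device benchmark in new people. Keep the test on later assessments as a separate, forward-in-time result.
3. Report Arm 2 as a cross-device validation, with AUC and calibration beside sensitivity and specificity. If Arm 1 is mixed, also show its results by watch model.
4. State in advance that absence of signal will not be concluded from Arm 2 alone.

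Features expressed as deviations from each wearer's own first weeks could be a sensitivity analysis only. They would remove a constant device offset, but they also discard differences in level between people, which may carry signal, and they use up the first weeks of data.

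The cost is some extra analysis work and a more qualified negative conclusion. The cross-validation would rest on about 92 people at most (184/2, assuming equal arms), so its estimates will be imprecise. No visit, device or participant procedure changes.

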**Study drop out mitigation strategies: .**

If the watch is not worn for 7 consecutive days while reporting to work, study staff will ask the study participant about any discomfort related to study participation, and will encourage them to continue to wear the watch to the extent they are comfortable (indicating that we may miss data such as sleep).

We have extensive experience conducting randomized controlled studies and have successfully employed these methods in our prior research.

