#### **E. Potential Scientific Problems:**

A potential problem is that participants wear the watches <50% of the time. This would render the data less usable for downstream analytics. Hence, we will monitor the smartwatch usage data on FitaBase, and if usage is <70%, we will request the participant to wear the watch as often or seek if there are any possible discomforts from the watches.

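### The 70% average wear goal does not hold missing sleep data to 30%: a participant with no sleep data can meet it and receive no prompt

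*Protocol*

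**What the plan says.** Section IV.C of the protocol lists five smartwatch streams to be collected: heart rate, respiration, stress, energy and sleep. It says that the analytic methods "can only handle data missingness up to 30" per cent. It then sets an incentive, a gift card worth $25, for reaching an average wear of 70% over the last three months of the study (March to May 2024). The goal and the analysis are linked directly: "The wear time goal reflects the threshold needed for data analysis. Wear time will be measured by the watch based on detected heart rate". No denominator is given for the 70% (all hours, waking hours or days), and there is no minimum per signal or per night.

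Three other places bear on this:

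- Section IV.C describes the watch as "operating with 18-hour battery life per charge cycle".
- The drop-out mitigation paragraph has staff approach a participant after seven consecutive days without wear while at work. It concedes that data may be lost when they encourage wear only as far as is comfortable ("indicating that we may miss data such as sleep").
- Section IV.E has staff monitor usage and act on the same cut-off: "if usage is <70%, we will request the participant to wear the watch as often".

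Section IV.F then trains the Aim 2 prediction models on the watch data and ranks predictors, keeping the top 10.

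**The concern.** The protocol treats average wear of 70% as the counterpart of at most 30% missing data. That works for a signal recorded evenly whenever the watch is on. It does not work for sleep, which is recorded only if the watch is worn in bed. The hours a participant is allowed to be off the wrist can all fall at night, so one stream can be wholly absent while the average looks adequate.

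What is at stake is Aim 2. If sleep features are missing by habit (for example, routine overnight charging) in participants who meet the wear goal, a low rank for sleep among the predictors could reflect non-measurement rather than absence of a signal. The shortfall arises during data collection, and nights that were never recorded cannot be recovered later.

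**Working it through.** **Inputs.** Wear goal 70%, tolerated missingness 30%, wear judged by heart rate and battery life 18 h are all from section IV.C. The prompt below 70% is from section IV.E. Assumptions: the 70% is taken over all 24 hours, and sleep lasts between 6 and 8 h. The documents state neither.

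**The plan's own figure.** 1 − 0.30 = 0.70, so the wear goal is the complement of the tolerated missingness, as the protocol says.

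**Permitted time off the wrist.** 0.70 × 24 = 16.8 h worn, which leaves 7.2 h a day off. A full night fits inside this allowance if sleep is 7.2 h or less.

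**Watch off for all sleep.** Wear share = (24 − sleep − waking hours off) / 24.

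| Sleep (h) | Worn all waking hours | 1 h off while awake |
|---|---|---|
| 6.0 | 75.0%, meets goal | 70.8%, meets goal |
| 6.5 | 72.9%, meets goal | 68.75%, fails |
| 7.0 | 70.8%, meets goal | 66.7%, fails |
| 7.2 | 70.0%, meets goal | 65.8%, fails |
| 7.5 | 68.75%, fails | 64.6%, fails |
| 8.0 | 66.7%, fails | 62.5%, fails |

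In every cell sleep is 100% missing, against a stated tolerance of 30%. The margin at 7 h is thin: 7.2 − 7.0 = 0.2 h, or 12 minutes a day off while awake. At 6 h it is 1.2 h.

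**Partial loss.** The 7.2 h limit applies only to complete loss. For an 8 h sleeper who wears the watch for all 16 waking hours and on a fraction f of nights, the goal requires 16 + 8f ≥ 16.8, so f ≥ 0.10. Up to 90% of nights could then be missing with the goal met.

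**Battery.** With one charge per 24 h (an assumption), 18 h of battery gives at most 18/24 = 75% wear. Some time off for charging is therefore built in, and taking it overnight is compatible with meeting 70%.

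**Do the other safeguards catch it?** The section IV.E prompt fires only below 70%, so it does not. The seven-day rule needs seven consecutive days without wear, and a watch worn every day and removed every night never meets that condition.

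**The denominator.** All hours is a reading favourable to the plan, because nights then at least count in the average. If the 70% referred to waking hours only, the goal would place no demand on nights at all.

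**The case against.** The strongest reply is that complete sleep loss passes only in a narrow band. It needs sleep of about 7.2 h or less and nearly unbroken waking wear, and one hour off while awake already fails at 6.5 h of sleep. The documents give no sleep or charging data, so nothing shows that the pattern is common. This stands as a limit on frequency. It does not restore the equivalence between 70% wear and 30% missingness, and partial loss well beyond 30% passes more easily.

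A second reply is that sleep loss is acknowledged and visible. The mitigation paragraph names it, newsletters report aggregate sleep and wear statistics, and the parser summarises features at fine time scales. This also stands, but none of it triggers action for an individual with adequate average wear and no nights. An analysis plan that is not shown may handle missingness by feature; it could not supply nights that were never recorded.

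Two stronger readings are tempting and should not be made:

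- **That a participant could be blank for the whole month before a survey and still meet the goal.** The arithmetic rules this out. March to May has 92 days, and a 28-day gap leaves at most 64/92 = 69.6% even with perfect wear otherwise. With 75% wear on the other days, the longest passing gap is 92 × (1 − 0.70/0.75) = 6.1 days. The seven-day rule also addresses long gaps while a participant is at work. In addition, section IV.F predicts outcomes in the following quarter and does not make the weeks just before a survey the predictor window.
- **That 70% wear admits a participant to the analysis.** The text makes it a condition for a gift card and a trigger for contact. It explains the goal by the analysis threshold but states no inclusion rule.

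**Conclusion.** The point holds for sleep and is conditional. An average of 70% heart-rate wear does not secure at most 30% missingness in the sleep stream, although the protocol offers it as reflecting that limit. On an all-hours reading, a participant who sleeps 7 h with the watch off and wears it otherwise scores 70.8%, has all sleep data missing and is not prompted. Complete loss requires sleep of about 7.2 h or less and essentially full waking wear. The number of participants affected cannot be estimated from the documents. The matter concerns one of the five streams used for Aim 2; the randomized comparison in Aim 1 rests on surveys and is not touched. It merits a change because the remedy is cheap and works only while data are being collected.

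**What to change.** - State the denominator of the 70% in sections IV.C and IV.E.
- Add a separate sleep criterion to the section IV.E monitoring prompt and to the incentive, computed from the Fitabase data already collected. A valid sleep record on at least 70% of nights would match the protocol's own 30% tolerance; the definition of a valid record should be written down.
- Advise participants to charge the watch during waking, sedentary time.
- Report missingness of sleep features separately when predictors are ranked, so that a low rank can be read against how much sleep was recorded.

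The cost is a wording change in the protocol and newsletter and a small addition to the existing parser. The downside is some more prompts to participants, and fewer who earn the incentive or count as adequate for sleep features.
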